**3.3.2 Withdrawal/drop-off as determined by the investigator**

The withdrawal decided by the investigator refers to the fact that the enrolled subjects are not suitable to continue the trial during the trial, and the investigator decides to withdraw from the trial.

1) During the trial, there are changes in the subject's condition, such as acute stent thrombosis, malignant arrhythmia, contrast nephropathy, acute left heart failure, hemodynamic instability, etc., which affect the compliance of continuing to participate in the trial or continue to participate in the trial may affect the safety of the subject, and the investigator believes that the patient should withdraw;

2) Patients with a definite diagnosis of PCI-related myocardial infarction at 48h;

3) Subjects who violate the inclusion/exclusion criteria, or have poor protocol compliance.

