**3.3 Criteria for the withdrawal of subjects from the trial**

**3.3.1 Subjects withdraw from the test on their own**

Patients can voluntarily withdraw from the trial at any time without providing any reason; or the subject has not explicitly withdrawn from the trial, but is no longer receiving LIPUS treatment or related indicators, it is also considered "withdrawal". Whenever possible, understand the reasons for the subject's withdrawal and document them in the case report form. Every effort should be made to keep the patient in the study and to continue with the required study-related treatments and markers.

For patients who voluntarily withdraw from the trial, the reason for withdrawal, the course of treatment, the time of the last treatment, and the results of the most recent test should be clearly recorded; The relationship between the branch or shedding in the trial and the trial should be carefully recorded, the possible impact of the discontinued case on the research conclusion should be analyzed, and the case report form should be completed and completed; Keep the original data of all exfoliated cases.

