**3.7.2 Intervention description**

Participants allocated to the intervention group will undergo a 10-day regimen utilizing a medical cardiovascular ultrasound therapy device (838C-M-L-I/II, Shenzhen, China). The ultrasound instrument is equipped with a sound head comprising five transducer units operating at an ultrasonic frequency of 0.84 MHz with a sound intensity range of 1 W/cm^2^–1.25 W/cm^2^. The therapeutic ultrasound sessions require a controlled environmental temperature. Patients will assume the supine position, exposing the precordial region, with the 5-pronged head positioned parallel to the heart’s long axis; it should cover the entire precordial region including the right and left coronary arterial trunks and the aortic root (Fig.1). The five transducer units function sequentially in a scanning pattern, with each unit operating for 5 seconds and transitioning with a 0.5-second interval, following a clockwise rotation until the treatment has been completed. The cardiovascular ultrasound therapy device operates in a pulsed mode, and each treatment session lasts for 20 minutes; there would be two daily sessions for a total of 20 treatments. The control group was not given extracorporeal cardiac ultrasound therapy. Participants in the control group will not receive cardiovascular ultrasound therapy. cardiovascular ultrasound therapy will be assessed at baseline (24th-hour post-PCI), on the 10th day, and at the end of the first and third months post-intervention. If it is necessary to change the medication regimen as much as possible, if it is necessary to change the medication regimen, it should be decided after evaluation by the investigator, and if the medication regimen that does need to be changed has an impact on the test results, the patient should be excluded and the reasons for changing the medication regimen should be recorded in detail.

[figure not shown]

Fig. 1. Diagram of ultrasound head placement.

A: Patients undergoing cardiovascular ultrasound therapy. B is used in patients with occlusion of one coronary artery and C is used in patients with occlusion of both coronary arteries.

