**3.9 Outcomes**

**3.9.1 Primary outcome**

The primary outcome measures will focus on the levels of hsCRP and interleukin-6 in the peripheral serum following 20 cardiovascular ultrasound therapy sessions (i.e., on the 10th day). Comparative analyses will be conducted between the cardiovascular ultrasound therapy intervention and control groups along with pre- and postintervention assessments.

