**(2) Serum markers of endothelial function**

The serum markers utilized to assess endothelial function encompass endothelial nitric oxide synthase (eNOS), endothelin-1 (ET-1), and vascular endothelial growth factor (VEGF) in the peripheral blood.

Monitoring of serum endothelial function will be conducted at baseline (24th hour post PCI); on the 5th and 10th days; and at the end of the 1st and 3rd months post intervention.

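### Section 3.3.2 item 1 allows withdrawal from the whole trial after serious clinical events, and no text secures the day 10, month 1 or month 3 data of these patients

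*Protocol*

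**What the plan says.** Section 3.3.2 of the protocol defines an investigator-decided withdrawal as the case where "the enrolled subjects are not suitable to continue the trial during the trial, and the investigator decides to withdraw from the trial". Item 1 applies this to changes in condition after enrolment: "acute stent thrombosis, malignant arrhythmia, contrast nephropathy, acute left heart failure, hemodynamic instability, etc". The event must either affect compliance or be such that to "continue to participate in the trial may affect the safety of the subject", and the investigator must judge that the patient should leave. Stopping ultrasound while staying in follow-up is not offered.

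Section 3.3.1, headed as withdrawal by the patient, contains the retention duty: "Every effort should be made to keep the patient in the study and to continue with the required study-related treatments and markers". Section 3.3.2 does not repeat it. Section 3.3.1 also counts as withdrawn a patient who "is no longer receiving LIPUS treatment or related indicators, it is also considered" a withdrawal.

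The primary outcome is hsCRP and interleukin-6 "following 20 cardiovascular ultrasound therapy sessions (i.e., on the 10th day"). Further assessments follow at months 1 and 3. Some measures also have a day 5 visit; the endothelial markers, for example, are taken after baseline "on the 5th and 10th days; and at the end of the 1st and 3rd months post intervention".

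Three other sections bear on the point:
- Section 6.3(2) has events recorded whether or not they relate to the ultrasound. Section 6.3(4) asks that patients who leave because of adverse reactions be followed up, with treatment and results recorded.
- Section 4 plans an intention-to-treat analysis.
- Section 4.3 plans three things: a comparison under plausible and extreme missing-data scenarios; after a significant primary result, an assessment of how strongly missingness would have to interact with group to remove significance; and multiple imputation if 10% or more of the baseline samples are excluded for missing data.

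**The concern.** Intention-to-treat needs an outcome from each randomised patient, including those whom a complication takes off treatment. Item 1 selects patients by a bad clinical course after enrolment, and its events bear directly on what the trial measures (inflammation, haemodynamics, ejection fraction, myocardial injury markers). If data collection ends with the withdrawal, the missing values are related to prognosis.

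Treatment is open to attending physicians and patients (section 3.5), so the person deciding may know the allocation, and the losses could differ between arms. At stake are the day 10 primary comparison and the month 1 and month 3 secondary outcomes. Data collection has to be settled in the protocol, because no analysis plan can recover a sample that was never drawn.

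**Working it through.** **1. Does any text keep the scheduled assessments after an item 1 withdrawal?**

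| Protocol text | What it covers | What it leaves open |
|---|---|---|
| 3.3.1, retention sentence | Effort to keep patients in and continue markers | Stands under voluntary withdrawal only |
| 3.3.1, records for leavers | Reason, treatment course, last treatment, latest test result, possible impact on the conclusion | No assessment after leaving |
| 6.3(2) | Recording of events, related or not | No outcome schedule |
| 6.3(4) | Follow-up of withdrawals due to adverse reactions | No duration, visit or sample named; an event attributed to the PCI may not count |
| 4 and 4.3 | Analysis of the data available | Not data collection |

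None secures day 10, month 1 or month 3. If assessments do stop at withdrawal, a patient withdrawn before day 5 loses all three post-baseline assessments (day 10, months 1 and 3), or all four for measures with a day 5 visit. A patient withdrawn after day 10 loses two of three, or two of four.

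**2. The plan's own figures.** Section 3.4: 160 / (1 − 0.20) = 200, as stated. The 160 cannot be reproduced because no SD is given. If a two-sample comparison of means was used (an assumption) with 80 per group, two-sided α = 0.05, 90% power and a 4 mg/L difference, the implied SD is

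SD = 4 / [(1.960 + 1.282) × √(2/80)] = 4 / (3.242 × 0.1581) ≈ 7.8 mg/L.

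**3. Size of the shift.** Let w_T and w_C be the proportions withdrawn in the ultrasound and control arms, and D the amount by which withdrawn patients would have fared worse than the rest, taken as the same in both arms. Each full-arm mean exceeds its completer mean by w × D, so the completer comparison is off by

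shift = (w_T − w_C) × D.

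The protocol gives neither w nor D. The values below are assumptions chosen to show a range.

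| Withdrawn per 100 (ultrasound v control) | D = 1 SD | D = 2 SD | In mg/L (× 7.8) | Share of 4 mg/L |
|---|---|---|---|---|
| 2 v 2 | 0 | 0 | 0 | 0% |
| 2 v 1 | 0.01 SD | 0.02 SD | 0.08 to 0.16 | 2% to 4% |
| 4 v 1 | 0.03 SD | 0.06 SD | 0.23 to 0.47 | 6% to 12% |

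For scale, the standard error of the difference with 100 per arm is √(2/100) = 0.141 SD, or about 1.1 mg/L. The largest shift shown is 0.06 / 0.141 ≈ 0.4 standard errors.

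**4. Which missing-data method would apply?** The unequal examples amount to 3/200 = 1.5% and 5/200 = 2.5% missing. The 10% trigger (20 of 200) counts every excluded sample, whatever the reason, so these shares alone do not settle whether multiple imputation would be used. The scenario comparison applies below the trigger too, and so does the interaction assessment if the primary result is significant.

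**The case against.** The strongest reply is that little is at risk. The population has elective PCI, infarction and procedural complications are excluded, and cardiac enzymes must be normal, so few such events should be expected. Section 4.3 is better than many plans: its interaction assessment is aimed at missingness that differs by arm. Section 6.3(4) does ask for follow-up, and no sentence says that assessments must stop. All of this stands, and it is why the point is modest. But these analyses test whether the primary conclusion survives the loss; they do not supply the missing values. Follow-up without a named visit or sample does not secure them either.

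Two stronger readings are tempting, and the documents support neither:
- A reader might infer that ultrasound patients will be withdrawn more readily on safety grounds, since "Participants in the control group will not receive cardiovascular ultrasound therapy". But the compliance ground applies to both arms, the safety ground concerns participation in the trial rather than ultrasound alone, and both arms had the PCI from which several listed events can arise. The protocol also does not say whether the deciding investigator is an unmasked attending physician. A difference between arms is possible, no more.
- A reader might take the sentence in section 3.3.1 as a rule that stopping ultrasound means leaving the trial. It stands under voluntary withdrawal and also refers to the related indicators. Read literally, it would count every control patient as withdrawn. It is weak support at most.

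**Conclusion.** The point holds as a gap in data collection. Section 3.3.2 item 1 permits withdrawal from the trial after prognostically important events, and no text secures the day 10, month 1 or month 3 data afterwards, so the intention-to-treat analysis may lack outcomes from these patients. The bias is probably small: about 0.1 to 0.5 mg/L for hsCRP under the unequal splits assumed above, and zero if losses are equal and alike in both arms. These figures rest on assumed withdrawal numbers, an assumed 1 to 2 SD worse outcome and an SD inferred from the sample size; the protocol states none of them. The case for acting is that the loss is avoidable at little cost and cannot be repaired later, not that the primary result is in doubt.

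**What to change.** Change the wording in three places:
- **Section 3.3.2:** state that an item 1 event in either arm may stop study treatment but does not end data collection for patients who still consent. Keep the day 10 blood sample where feasible, on the calendar day and whatever number of sessions was given. Keep the month 1 and month 3 assessments, reduced to vital status, serious events and symptoms if the patient is too ill.
- **Retention duty:** extend the sentence in 3.3.1 to 3.3.2.
- **Section 6.3(4):** state that follow-up runs to month 3 whatever the judged cause.

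The decision to stop treatment stays with the investigator, and tabulation can be left to the SAP. The visits are already scheduled, and section 4.3 expects all participants to be inpatients during treatment, so the day 10 sample needs no extra visit for those still in hospital. The downside is that sites must contact a few more, sicker patients at months 1 and 3.

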**3.2.2 Exclusion Criteria:**

• ST-segment elevation myocardial infarction and non–ST-segment elevation myocardial infarction;

• Occlusion of branch vessels during PCI;

• Perioperative use of hormones or immunosuppressants;

• Combined infection or other inflammatory diseases;

• Postoperative fever;

• Allergy to contrast media or cardiovascular ultrasound acoustic head–related materials;

• Changes in lipid-lowering, antiplatelet, and antihypertensive drug regimens during treatment;

• A clear diagnosis of autoimmune disease;

• A history of other surgeries or trauma in the preceding 7 days;

• Infection with the novel coronavirus during the preceding month;

• Previous PCI treatment;

• Previous cardiovascular ultrasound treatment;

• Diabetes mellitus.

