**4** **Statistical analysis**

The baseline characteristics of both groups will be summarized using appropriate descriptive statistics. Analysis of both primary and secondary outcomes will be based on the intention-to-treat approach, ensuring that all participants remain assigned to their original group throughout the study.

Normally distributed data will be presented as the mean (standard deviation), and non–normally distributed data will be depicted as the median (interquartile range). Group comparisons will be conducted using independent sample tests, and within-group comparisons before and after treatment will be evaluated using paired sample tests. Clinical symptom variables will be portrayed as percentages. Categorical data will be assessed using either the chi-squared test or Fisher’s exact test. A significance level of.05 will be employed to interpret the P values. The statistical analysis will be conducted utilizing SPSS version 26 statistical software (IBM, Armonk, NY).

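### Section 3.3.2 item 3 lets enrolled patients be withdrawn for eligibility violations without securing their day-10 hsCRP and IL-6, and two undated criteria may extend this to post-randomisation inflammation

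*Protocol*

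**What the plan says.** - **Withdrawal (Protocol 3.3.2).** Investigator withdrawal is for cases where "the enrolled subjects are not suitable to continue the trial during the trial". Item 1 covers changes in the patient's condition, item 2 covers PCI-related infarction, and item 3 covers "Subjects who violate the inclusion/exclusion criteria" or poor compliance.
- **Exclusion list (3.2.2, repeated in the synopsis).** It includes "Postoperative fever" and "Combined infection or other inflammatory diseases", neither with a reference time. It also includes "Changes in lipid-lowering, antiplatelet, and antihypertensive drug regimens during treatment", which describes something that happens once treatment is under way.
- **Timing (3.9.1 and 3.9.2(3)).** Baseline is the 24th hour after PCI. The primary outcome is hsCRP and IL-6 on day 10, after 20 sessions.
- **Masking (3.5).** Attending physicians and patients know the allocation. Only the team members collecting primary outcome data are masked.
- **Analysis (4 and 4.3).** Section 4 promises intention-to-treat, "ensuring that all participants remain assigned to their original group throughout the study". Section 4.3 adds plausible and extreme missing-data scenarios, a check of how strong an arm-by-missingness interaction would overturn a significant result, and multiple imputation once 10% or more is missing.
- **A second removal rule (3.7.2).** A patient whose medication change affects the results is to be excluded.

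**The concern.** Intention-to-treat needs two things: patients analysed in the arm to which they were randomised, and an outcome for each of them. Section 4 secures the first. Item 3 of 3.3.2 puts the second at risk, because a patient withdrawn before day 10 may have no primary value.

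The reason for withdrawal matters here. Fever and infection are acute inflammation, and the primary outcome measures inflammation. If item 3 is applied to a fever or infection arising after randomisation, missingness depends on the value that would have been observed, and the decision may rest with someone who knows the arm. Unequal removal biases the comparison. Removal by one common standard can shrink a real effect.

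**Working it through.** **1. Does the text reach past enrolment?**
- 3.3.2 concerns enrolled patients, so item 3 operates after enrolment.
- The drug-regimen criterion in 3.2.2 and the exclusion rule in 3.7.2 both concern events during treatment, so neither the list nor the practice of exclusion stops at screening.
- The fever and infection items state no reference time. The text does not say when randomisation falls relative to PCI and the 24-hour baseline (the flowchart is not shown).
- Removal for a fever or infection before day 10 is therefore a permitted reading. It is not the only one.

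**2. Is the day-10 sample protected elsewhere?**
- 3.3.1 asks for efforts to keep patients in the study and continue the required markers, but in the context of self-withdrawal. 3.3.2 has no counterpart.
- 6.3(4) asks for follow-up of patients withdrawn for adverse reactions but does not mention hsCRP or IL-6.
- Section 4 fixes group assignment, not outcome collection.

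**3. The plan's own sample size (3.4).** 160/(1 − 0.20) = 200, as stated. No SD is given. Solving the two-sample formula backwards (difference 4 mg/L, two-sided α 0.05, power 90%, 80 per group):

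SD = 4 / [(1.960 + 1.282) × √(2/80)] ≈ 7.8 mg/L.

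This is an assumption for what follows. Nothing here disputes the 200.

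**4. Illustration with no true effect.** Assume day-10 hsCRP is normal with SD 7.8 and that the highest fraction f of an arm is removed. The arm mean then falls by SD × φ(z)/(1 − f), where z is the 1 − f quantile.
- f = 8%: z = 1.405, φ = 0.1487; fall = 7.8 × 0.1487/0.92 = 1.26 mg/L.
- f = 2%: z = 2.054, φ = 0.0484; fall = 7.8 × 0.0484/0.98 = 0.39 mg/L.
- Spurious difference = 1.26 − 0.39 ≈ 0.87 mg/L.

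A lognormal with mean 10 and SD 7.8 gives about 1.03 mg/L. If only half the removals track hsCRP, simulation gives about 0.5 to 0.7 mg/L.

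Other splits under the normal model:

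| Ultrasound removed | Control removed | Spurious difference (ultrasound − control) |
|---|---|---|
| 8% | 2% | −0.87 mg/L |
| 2% | 8% | +0.87 mg/L |
| 4% | 2% | −0.32 mg/L |
| 5% | 5% | 0 |

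**5. Illustration with a true effect of −4 mg/L.** Use one common removal threshold in both arms and 80 per group. If 5%, 10% or 20% of controls exceed it, then 1.5%, 3.6% or 8.8% of the ultrasound arm do. The observed effect becomes −3.46, −3.12 or −2.63 mg/L, and power falls from 90% to about 84%, 79% or 68%.

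**6. Would 4.3 catch it?** With 100 per arm, 8% and 2% removal loses 8 + 2 = 10 of 200 patients, or 5%. That is below the 10% trigger, so multiple imputation would not start.

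**The case against.** The strongest reply is that the criteria are screening criteria. Section 3.1 applies them before inclusion. Inclusion requires TIMI flow after PCI, so enrolment follows the procedure and a postoperative fever has a natural window from PCI to enrolment. Where the authors meant an in-trial event they said so, in the drug-regimen item. In 3.3.2, changes in condition come under item 1, so item 3 most naturally means patients enrolled in error. This stands as a plausible reading, perhaps the commoner one. It does not remove the narrower problem: patients found ineligible after randomisation can still be withdrawn with no stated provision for their primary outcome.

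A reader might go further in four ways that the documents do not support.
- **That the plan requires removal of anyone with fever or infection up to day 10.** The text permits that reading but does not prescribe it. The look-back windows on other items ("A history of other surgeries or trauma in the preceding 7 days", "Infection with the novel coronavirus during the preceding month") do not settle it, because they limit prior history and say nothing about later events.
- **That the trial is tilted towards the device.** The protocol's own hypothesis, less inflammation under ultrasound, would predict fewer removals in that arm. Reversing the split reverses the sign. The 8% and 2% have no source in the documents.
- **That withdrawal flatly contradicts intention-to-treat.** Withdrawal from the trial is not stated to be removal from the analysis. The conflict arises through uncollected outcomes.
- **That a device-related fever would go unrecorded.** Section 6.3 requires adverse reactions to be recorded whether or not related to treatment, and withdrawals due to adverse reactions to be followed up.

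The scenario and interaction analyses in 4.3 are a real safeguard against over-reading a significant result. They show how fragile it is, but they cannot restore values that were never measured.

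**Conclusion.** The point holds in limited form. Item 3 of 3.3.2 allows possibly unmasked withdrawal of enrolled patients for eligibility violations, the day-10 hsCRP and IL-6 samples are not secured, and this weakens the intention-to-treat commitment. The undated fever and infection criteria make it possible, not certain, that such withdrawals track the outcome itself.

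Neither size nor direction can be fixed from the documents. The 0.9 to 1.0 mg/L shift is about a quarter of the 4 mg/L target (0.87/4 = 22%; 1.03/4 = 26%). It rests on an SD that the protocol does not state, assumed removal rates, removal of the very highest values, and a comparison of patients with data only. Equal removal with no true effect gives no bias. The matter merits correction because an analysis plan cannot recover samples that the protocol lets sites leave uncollected, and the correction is cheap.

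**What to change.** 1. In 3.2.2 and the synopsis, state that the fever and infection criteria are judged up to randomisation.
2. In 3.3.2 item 3, record eligibility violations found after randomisation as protocol deviations. Still collect the day-10 and later samples and keep the patient in the intention-to-treat analysis. Leave any decision on continuing treatment to the investigator.
3. Reconcile this with the exclusion rule for medication changes in 3.7.2, so that the two sections and section 4 agree on who is followed and analysed.
4. Report any analysis omitting patients with post-randomisation fever or infection only as a sensitivity analysis, defined by the date of the event and not by arm or result.

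The cost is a wording amendment and one sensitivity analysis; the 200 is unchanged. The downside is that a few high values stay in the primary comparison and slightly widen its interval.
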